| Laboratory operation / evaluation                           |            |                  |     |     |     |     |                  |                                              |                                    |                                            |
| Pregnancy test                                 | ×          |                  |     |     |     |     | ×                |                                              |                                    |                                            |
| Routine blood test                             | ×          | ×                | ×   | ×   | ×   | ×   | ×                | ×                                            |                                    |                                            |
| Biochemical routine                            | ×          | ×                | ×   | ×   | ×   | ×   | ×                | ×                                            |                                    |                                            |
| Urine routine                                  | ×          | ×                | ×   | ×   | ×   | ×   | ×                | ×                                            |                                    |                                            |

|                                                 |   |   |   |   |   |   |   |   |   |  |
|-------------------------------------------------|---|---|---|---|---|---|---|---|---|--|
| Stool routine                      | × | × | × | × | × | × | × | × |   |  |
| Coagulation function               | × | × | × | × | × | × | × | × |   |  |
| Thyroid function                   | × | × | × | × | × | × | × | × |   |  |
| Plasma amylase/lipase              | × | × | × | × | × | × | × |   |   |  |
| Pulmonary function                 | × |   |   |   |   |   |   |   |   |  |
| Hepatitis B detection              | × |   |   |   |   |   | × |   |   |  |
| HBV-DNA                            | × | × | × | × | × | × | × | × |   |  |
| EBV-DNA                            | × | × | × | × | × | × | × | × |   |  |
| Efficacy evaluation                             |   |   |   |   |   |   |   |   |   |  |
| Radiography examination            | × |   | × |   | × |   | × |   | × |  |

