17. Radiography evaluation: according to RECIL 2017 lymphoma criteria, the efficacy was evaluated by the researchers. During the screening period and every 6 weeks after the start of the study, enhanced PET / CT or MR or CT examinations were performed in the head and neck (including nasal cavity, hard palate, anterior cranial fossa and nasopharynx), chest, abdomen and pelvis; If you are allergic to CT contrast medium, enhanced MRI can be used. The whole body PET / CT or MR or CT examinations were performed in the screening period, 6, 12, 18 weeks after treatment, repeated every 8 weeks after 6 cycles up to 12 months. Additional PET / CT examination is required if residual lesions or suspicious progression are indicated during enhanced CT follow-up. Except for the subjects who stopped using drugs due to the progress of disease determined by imaging evaluation, imaging evaluation was continued according to the established time until the occurrence of imaging disease progression, the start of new anti-tumor treatment, withdrawal of informed consent, death or the end of the study (whichever occurs first). Within 24 months after the end of the treatment, imaging reexamination was carried out every 12 weeks, and over 24 months, reexamination was carried out every 12-24 weeks.
18. Bone marrow puncture / biopsy: bone marrow puncture / biopsy should be performed in the screening stage and when CR was judged by imaging; If it is not clear whether the bone marrow is invaded under the microscope, flow cytometry or immunohistochemistry can be performed according to the judgment of the researcher. Patients with bone marrow involvement should be reexamined every 6 weeks.
19. Biomarker detection: before each cycle of treatment.

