Patients will receive efficacy measurements, including ORR, PFS, OS, duration of response (DoR). During the entire study, efficacy will be evaluated based on International Working Group consensus response evaluation criteria in lymphoma (RECIL 2017). Patients underwent CT, MRI or whole body  $^{18}\text{F}$ -fluorodeoxyglucose (FDG) PET scans before the first treatment and then every 6 weeks up to cycle 6, and every 12 weeks thereafter. A whole-body PET scan was strongly recommended. Efficacy evaluation will be performed every 2 treatment cycles (i.e. 6 weeks) until the completion of 6 cycles of treatment, repeated every 8 weeks after 6 cycles up to 12 months, or disease progression, intolerable toxicity, death, investigators' decision, or the patient's voluntary withdrawal from the study (whichever occurs first).

Safety observation indicators include monitoring and recording of adverse events (TEAE and SAE) during treatment, performing laboratory tests (including blood routine, biochemical and urine tests), 12-lead electrocardiogram, and vital signs as specified in the design. Adverse events will be evaluated according to the NCI CTCAE (version 5.0). The safety and tolerability of the research drugs will be evaluated through laboratory and auxiliary examinations, physical and vital signs examinations. The design and flow chart of this study are shown in **Figure 1**.

[figure not shown]

Figure1. Flow chart of this study

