## **6.2 Visits during the treatment period**

1. Vital signs.
2. Physical examination.
3. Weight measurement.
4. Laboratory examination: Before each medication administration during the treatment period, the laboratory examination must be completed and the blood sampling time should not be earlier than 48 hours before the medication. Only when the investigator determined the laboratory examination results qualified can the subjects continue medication. During the treatment period, the investigator can increase the frequency of blood routine examinations

according to the conditions of the subjects.

5. Plasma EBV-DNA monitoring: Monitored on the first cycle of treatment and the first day of subsequent cycle. After all treatment courses are completed, monitored once a month at a fixed time.
6. 12-lead electrocardiogram: Evaluated every 3 weeks ( $\pm 3$  days) from the first administration.
7. Cardiac ultrasound examination (including evaluation of left ventricular ejection function): evaluation will be carried out every 12 weeks ( $\pm 7$  days) from the first administration.
8. Thyroid function: Evaluated every 3 weeks ( $\pm 3$  days) from the first administration.
9. Pulmonary function: Evaluated every 12 weeks ( $\pm 7$  days) from the first administration or there may be clinical needs.
10. Bone marrow examination (smear  $\pm$  biopsy): Evaluated every 6 weeks ( $\pm 7$  days) from the first administration for those with bone marrow infiltration or there may be clinical needs.
11. Tumor evaluation: Baseline and follow-up evaluations should adopt the same radiological methods and be performed by the same investigator as far as possible. Tumor assessment will be calculated according to the actual date of medication before each medication and will be evaluated every 6 weeks ( $-7$  days), regardless of the effect of drug withdrawal. For patients who are suspected of developing PD before the next scheduled evaluation, an extra tumor evaluation should be performed.
12. Administration of the research drug: Administered every 3 weeks. If the subject cannot take the medicine at the planned time due to special reasons

(such as adverse reactions), a maximum delay of 14 days is allowed.

13. Record the combined medication;

14. Record AE.

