## **7.2 Evaluation of efficacy**

The efficacy of the study drug will be determined by the objective tumor evaluation made by the research center based on the RECIL 2017 Response Criteria for Malignant Lymphoma.

Radiological evaluation of tumor is determined by PET/CT, MR or CT with uniformity in evaluation method as well as machine and technical parameters throughout the study period. Unless contraindications, contrast agents should be used. The radiological results are interpreted by researchers or radiologists in each research center. If the tumor evaluation has been performed within 21 days before enrollment with the same method and machine in the same hospital, it can be used as a baseline tumor evaluation. The baseline tumor evaluation should include the nasal cavity, chest, abdomen, pelvis and any other suspected areas. If there are clinical indications, appropriate methods, such as cranial MRI, bone scan can be used to examine any other known or suspected disease sites.

From the day of the first administration, radiological examination will be performed to evaluate the tumor condition every 6 weeks (-7 days) until the completion of 6 cycles of treatment, PD, intolerable toxicity, death, investigator's decision or patient's voluntary withdrawal from the study (whichever occurs first). Repeated every 8 weeks after 6 cycles up to 12 months, or disease progression, intolerable toxicity, death, investigators' decision, or the patient's voluntary withdrawal from the study. Researchers can arrange additional radiological examinations based on the patient's clinical conditions. If the medication is suspended due to AE or other reasons, the tumor evaluation will still be carried out as originally planned. For patients who are suspected of developing PD before the next scheduled tumor evaluation, an unscheduled tumor evaluation should be performed.

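### Three incompatible on-treatment imaging intervals after cycle 6 (6-, 8- and 12-weekly) leave the dating of PFS and DoR to the section a site follows

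*Protocol*

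**What the plan says.** The imaging interval after cycle 6 is given in four places.

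- **Section 3.1, imaging sentence:** scans are done "before the first treatment and then every 6 weeks up to cycle 6, and every 12 weeks thereafter".
- **Section 3.1, same paragraph, two sentences later:** efficacy evaluation is every two cycles "until the completion of 6 cycles of treatment, repeated every 8 weeks after 6 cycles up to 12 months".
- **Section 7.2:** 6-weekly from the first administration through six cycles, then "Repeated every 8 weeks after 6 cycles up to 12 months".
- **Study flow chart, note 17:** the first part has regional scans "During the screening period and every 6 weeks after the start of the study", with no later change. The second part has whole-body scans at weeks 6, 12 and 18 and then 8-weekly to month 12.
- **Section 6.2, item 11:** every 6 weeks during treatment, with no change after cycle 6.

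The flow-chart row "Radiography examination" has crosses at screening, cycles 2 and 4, end of treatment and radiography follow-up. The column for cycles 5 to N is blank. The row refers the reader to note 17.

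The starting point for counting is also worded differently. Section 7.2 counts from the first administration. Section 3.1 counts in pairs of cycles and equates a pair with 6 weeks. Section 6.2 says "Tumor assessment will be calculated according to the actual date of medication before each medication", and the same sentence goes on to say that drug withdrawal makes no difference. Section 7.2 adds: "If the medication is suspended due to AE or other reasons, the tumor evaluation will still be carried out as originally planned". Section 5.5 likewise keeps imaging to plan in the long suspensions it describes.

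**The concern.** RECIL evaluation needs imaging, so the 12-weekly and 8-weekly sentences of section 3.1 cannot both be followed, and neither fits the unchanging 6-weekly rule of section 6.2. A site can comply with one section and deviate from another.

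Progression found on imaging is dated by the scan that shows it. Under section 10.2, patients without an event are censored at the last tumour evaluation. PFS and DoR are named secondary endpoints in a multicentre, investigator-assessed, single-arm trial, so no control arm shares the scan timing. If centres follow different sections, the pooled Kaplan-Meier curves mix calendars. The date of a late CR, and of the confirmation that section 10.4 requires when it asks for a confirmed ORR, would move in the same way. Scans that were not done on time cannot be recovered at analysis.

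**Working it through.** **Step 1: the part on which the text agrees.** Two cycles of 3 weeks make 6 weeks, so six cycles give 2×3, 4×3 and 6×3, that is weeks 6, 12 and 18. This reproduces the weeks listed in note 17, and every text version agrees to this point.

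**Step 2: run each interval from week 18 to week 52.**

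| Interval after week 18 | Where stated | Further scan weeks | Number |
|---|---|---|---|
| 6-weekly | 6.2; note 17, first part | 24, 30, 36, 42, 48 | 5 |
| 8-weekly | 3.1; 7.2; note 17, second part | 26, 34, 42, 50 | 4 |
| 12-weekly | 3.1 | 30, 42 | 2 |

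Week 42 is the only later date common to all three. A response first seen at week 18 would next be scanned at week 24, 26 or 30.

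**Step 3: mean detection delay after week 18.** Assumptions:
- PFS is exponential with a median of 7.0 months, the protocol's own figure for chidamide (section 10.1).
- All progression is found at scheduled scans.
- Each interval simply continues.

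7.0 months × 52.1775/12 = 30.44 weeks, so λ = ln 2 / 30.44 = 0.02277 per week and 1/λ = 43.92 weeks. The share event-free at week 18 is exp(−0.02277 × 18) = 0.664. Because the exponential has no memory, the mean delay with interval D is D / (1 − exp(−λD)) − 1/λ:

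- D = 6: 6 / 0.1277 − 43.92 = 3.1 weeks
- D = 8: 8 / 0.1665 − 43.92 = 4.1 weeks
- D = 12: 12 / 0.2391 − 43.92 = 6.3 weeks

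**Step 4: observed median.** This is the first scan at or after the true median. Scan weeks are from step 2, with an end-of-treatment scan assumed at week 52.

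| True median (weeks) | 6-weekly | 8-weekly | 12-weekly | Spread |
|---|---|---|---|---|
| 17.4 (4 months) | 18 | 18 | 18 | 0 |
| 26.1 (6 months) | 30 | 34 | 30 | 4 |
| 30.4 (7 months) | 36 | 34 | 42 | 8 |
| 39.1 (9 months) | 42 | 42 | 42 | 0 |
| 43.5 (10 months) | 48 | 50 | 52 | 4 |

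The 8 weeks at 7 months is the largest spread for any true median between weeks 18 and 48. The order is not even monotone: at 7 months the 8-weekly calendar gives an earlier median than the 6-weekly one. The mean delays in step 3 are therefore the fairer measure.

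**The case against.** The 8-weekly version appears in three places, and the 12-weekly phrase may have strayed from the post-treatment rule in note 17, which is also 12-weekly. On that view this is an editing slip. As written, though, the phrase starts after cycle 6, during treatment, and it does not explain the unchanging 6-weekly rule.

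The size is also open to challenge. Sections 6.2 and 7.2 call for an extra scan when progression is suspected, which shortens the delays. Patients off treatment move to 12-weekly follow-up imaging, so the on-treatment calendars do not apply to everyone. Both points stand, and the figures are illustrative.

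A reader might infer more than the documents support:

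- **A fourth schedule with no scans after week 12.** The blank 5-N column belongs to a row that cites note 17, and that note prescribes the later scans. It is a missing cross.
- **Scans that drift with toxicity.** If scans followed dosing and each of the five later cycle starts slipped by the permitted 14 days, the end of cycle 6 would move from week 18 to week 28 (18 + 5 × 2). But sections 5.5, 6.2 and 7.2 all say that interrupting the drug does not move the scans. The anchor wording is unclear; the sections do not set opposed rules.
- **An effect on the primary result.** The text agrees to week 18, and sections 3.3, 5.1.1 and 5.1.2 take patients with SD or PD off study, so later on-treatment scans fall mainly on responders. Late conversion from minor response, which that rule does not name, is a small residual.
- **A distorted comparison with historical PFS.** The benchmark rates in section 10.1 are for ORR; no PFS comparison is planned.

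**Conclusion.** The contradiction is real and lies in current text: three on-treatment intervals after cycle 6, two of them in one paragraph, plus a flow-chart row that does not match its own note and an unclear anchor. It affects PFS and DoR dates, and the timing of late CR or confirmation, after week 18. The primary ORR and the Simon stage-1 decision are essentially untouched.

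Under the step 3 assumptions, going from 6-weekly to 12-weekly scans adds about 3.2 weeks (6.3 − 3.1) to the mean detection delay among patients still event-free at week 18. The gap between observed medians runs from 0 to 8 weeks and depends on where the true median falls, so no single value should be quoted as the bias. The point should be fixed, but it does not put the trial's main conclusion at risk.

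**What to change.** Reconcile section 3.1, both parts of note 17, section 6.2 and section 7.2 to one calendar in identical words, counted from the first dose. The version stated most often is weeks 6, 12 and 18, then every 8 weeks to month 12. If the sponsor keeps it:

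- delete the 12-weekly clause in section 3.1;
- give the open-ended 6-weekly wording in section 6.2 and the first part of note 17 an end at week 18;
- remove the reference to the actual medication date in section 6.2, keeping the statement that interruption does not move scans;
- mark week 18 and the later scans in the 5-N column of the flow chart.

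The cost is wording in four places and one flow-chart row. It adds no scans beyond those section 7.2 already requires. A site that had been working to 12 weeks would do two more by week 52 (4 instead of 2).

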### 3.2 Screening Period

Informed consent must be obtained for each patient and documented with a signed informed consent form (ICF) prior to any study procedures. The screening period is from 28 days to 1 day prior to the start of the study drug. The screening assessments should be performed within this period in order to assess the eligibility of the patient against the inclusion and exclusion criteria.

### 3.3 Treatment Period

In phase Ib, patients received oral escalating doses of chidamide (20, 25, 30 mg) twice a week continuous and fixed doses of 200mg sintilimab intravenously over a period of 30–60 min, once every 21 days. If DLTs does not occur, the established dose escalation plan could be proceeded to the next level. If one case of DLT occurs, 3 more subjects should be added to this dose level until there is no new DLT report. If there are more than 2 cases of DLT, the forward dose level of this dose level is defined as MTD. The dose level of Sintilimab is 200 mg (fixed dose) each time and repeated every three weeks. Patients that achieved CR and PR could receive for up to one-year treatment. Patients defined with SD and PD should withdraw from the study.

The phase II study is proceeded according to the RP2D of Chidamide. Patients that achieved CR and PR could receive for up to 12 months treatment, otherwise until disease progression, death, intolerable toxicity, completion of the scheduled treatment cycle, or the investigators' decision to withdraw (whichever occurs first).

### **3.4 End of Treatment**

End of Treatment visit (EOT) should be performed as soon as possible after the decision to discontinue the study drug, preferably within 30 days after last dose of study drug and before initiation of any new anticancer treatment.

### **3.5 Follow-up Period**

All patients, regardless of disease status, will be visited for end of treatment within 4 weeks after the end of the study, followed every 12 weeks for up to 3 years, or until withdrawal of consent, loss to follow-up, or death, whichever occurs first. When disease assessments are not planned for a follow-up visit, the visit can be done by phone.

### **3.6 End of Study**

The study will be ended 8 weeks after the last medication of the last enrolled patient or when the disease progresses (except for the withdrawal of ICF).

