|                                                 | interference in safety/ efficacy evaluation of the study drug as judged by the investigator.                                                                                                                                                                                                                                                                                                                                                                                                                                                                                                                                                                                                                                                                                                                                                                |
| Established treatment and study duration | 
The duration of the study subjects is defined as the time from the date of first dosage of sintilimab plus chidamide to the completion of the follow-up period, withdrawal of consent, loss to follow-up, or death, whichever occurs first.
 
The study will include a screening period (of up to 28 days), a treatment period (cycles of 3 weeks, up to 1 year), and a follow-up period (approximately every 12 weeks visits for up to 3 years after treatment discontinuation).
 
Treatment after 1 year, patients can continue sintilimab plus chidamide, or autologous hematopoietic stem cell transplantation (ASCT) as consolidation, or stop treatment and observation.
 
The end of study occurs at the last visit or last scheduled procedure for the last patient, unless the study is terminated earlier by investigators.
 |

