## Schedule of assessments

## Study flow chart

| Study period                                                | Screening  | Treatment period |     |     |     |     |                  | Follow-up period
(up to 3 years from EOT) |                                    |                                            |
|-------------------------------------------------------------|------------|------------------|-----|-----|-----|-----|------------------|----------------------------------------------|------------------------------------|--------------------------------------------|
|                                                             | Screening  | 1                | 2   | 3   | 4   | 5-N | EOT  | Safety follow up                 | Radiography follow up  | Survival follow up             |
| Visit time and window period                                | D-28 to -1 | ±3d              | ±3d | ±3d | ±3d | ±3d | +28d             | 30 days after the last treatment ± 3days     |                                    | 12 weeks after the last treatment ± 7 days |
| Study management process                                    |            |                  |     |     |     |     |                  |                                              |                                    |                                            |
| Informed consent                                            | ×          |                  |     |     |     |     |                  |                                              |                                    |                                            |
| Eligibility criteria                                        | ×          |                  |     |     |     |     |                  |                                              |                                    |                                            |
| Demography                                                  | ×          |                  |     |     |     |     |                  |                                              |                                    |                                            |
| Medical/Cancer history                          | ×          | ×                | ×   | ×   | ×   | ×   | ×                | ×                                            |                                    |                                            |

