## **6.5 Follow-up of overall survival**

For patients who have already progressed and started other new treatments, survival follow-up will be carried out every 8 weeks ( $\pm 7$  days) and the following anti-tumor treatment information and survival data of the patients will be collected until 2 years after the first administration.

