### **7.1.2 Secondary outcome measures**

1. Progression-Free Survival (PFS) time.

2. Duration of Response (DoR).
3. DoR: Among participants who experience an objective response, DoR is defined as the date of their first objective response (which is subsequently confirmed) to disease progression or among participants who experience an objective response.
4. Overall survival refers to the time from the beginning of randomization to death due to any reason.
5. The frequency and severity of adverse events (Adverse Event, AE) and the frequency of severe adverse events (Severe Adverse Event, SAE) (CTCAE v5.0).
6. To Explore biomarkers that may have predictive effects.

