#### **10.4 Efficacy analysis**

The researcher can decide the patient's treatment plan based on the efficacy assessment made by the research center. Please refer to Chapter 7.1 for the definition of each efficacy endpoint. The confirmed ORR and the 95% Clopper Pearson confidence interval should be calculated. In addition, other efficacy endpoints, including PFS, DCR, DoR and OS should also be evaluated.

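### The end-of-study and survival follow-up rules in 3.6 and 6.5 contradict the 3-year follow-up planned elsewhere and would truncate PFS, DoR and OS; OS and DoR are also wrongly worded in 7.1.2

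*Protocol*

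**What the plan says.** **End of study.** Protocol 3.6: "The study will be ended 8 weeks after the last medication of the last enrolled patient or when the disease progresses". The synopsis differs: "The end of study occurs at the last visit or last scheduled procedure for the last patient". It plans "a follow-up period (approximately every 12 weeks visits for up to 3 years after treatment discontinuation". The flow chart heads the follow-up columns "up to 3 years from EOT". Section 3.5 follows all patients, whatever their disease status, every 12 weeks for up to 3 years.

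**PFS and OS follow-up.** Section 6.4 starts PFS follow-up 8 weeks after the last dose and stops it, at the latest, when the entire study ends. Section 3.1 stops OS follow-up at termination of the entire study. Section 6.5 covers patients who have progressed and started new treatment, and collects survival "until 2 years after the first administration".

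**Definitions.** Section 7.1.2: "Overall survival refers to the time from the beginning of randomization to death due to any reason". Its DoR sentence breaks off after progression and names no second event; the same broken sentence stands in the synopsis and in the section 2 table. Section 10.2 runs OS from first medication, and DoR from first CR or PR to progression or death. Section 10.4 says: "Please refer to Chapter 7.1 for the definition of each efficacy endpoint".

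**Imaging after cycle 6.** One sentence of 3.1 gives "every 6 weeks up to cycle 6, and every 12 weeks thereafter". A later sentence of 3.1, flow chart note 17 and section 7.2 give 8 weeks, up to 12 months. Section 6.2 gives 6 weeks without addressing the period after cycle 6.

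**The concern.** Long-term survival is the first secondary objective, and PFS, DoR and OS are the endpoints that serve it. Three current sections give incompatible answers on when observation stops, and the 6.4 and 3.1 stopping rules take over whatever end of study is applied. A site following 3.6 or 6.5 would stop collecting data that 3.5 and the flow chart expect.

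The 2-year stop in 6.5 falls on patients who have progressed and moved to new treatment, where many of the deaths are to be expected. If the progression clause in 3.6 is read patient by patient, survival after progression is not collected at all.

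Separately, 10.4 sends the reader to the section with the defective OS and DoR wording, and recorded progression dates depend on which scan interval a site uses.

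**Working it through.** **Inputs.** Planned treatment is up to 1 year (synopsis). The study closes 8 weeks after the last enrolled patient's last dose (3.6). PFS follow-up begins 8 weeks after the last dose (6.4). Follow-up runs to 3 years after treatment (synopsis, flow chart, 3.5). Survival collection stops 2 years after first dose (6.5). One month is taken as 30.4375 days, so 8 weeks = 56 / 30.4375 = 1.84 months.

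**Step 1: the last enrolled patient under 3.6.** With T months on treatment:
- observation ends at T + 1.84 months from first dose under 3.6;
- it ends at T + 36 months under the 3-year rule;
- the difference is 36 − 1.84 = 34.16 months, whatever T is.

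For T = 12 this is 13.84 against 48 months. The lost period corresponds to the whole post-treatment programme: 36 × 30.4375 / 84 = 13.04, or about 13 twelve-weekly visits. Because 6.4 starts at the moment 3.6 closes the study, this patient has no PFS follow-up visits.

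**Step 2: earlier enrollees under 3.6.** A patient whose last dose came d months before the last enrolled patient's last dose loses max(0, 34.16 − d) months: about 22.2 for d = 12, about 10.2 for d = 24, and nothing from about d = 34.2.

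**Step 3: the 6.5 stop.** Loss against 3 years after treatment = (T + 36) − 24 = T + 12 months.

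| Time on treatment T (months) | 3-year rule ends at | 6.5 ends at | Loss |
|---|---|---|---|
| 1.4 | 37.4 | 24 | 13.4 |
| 6 | 42 | 24 | 18 |
| 12 | 48 | 24 | 24 |

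**Step 4: what the truncation could hide (illustration only).** Assume exponential PFS at the 7.0-month median that section 10.1 cites for chidamide alone. The share still event-free at 13.84 months is 0.5^(13.84/7.0) = 0.254, about 25%, and these patients would be censored there. The protocol gives no OS median, so a range is assumed, with share alive = 0.5^(t/median):

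| Assumed OS median (months) | Alive at 13.8 months | Alive at 24 months | Alive at 48 months |
|---|---|---|---|
| 12 | 45% | 25% | 6% |
| 18 | 59% | 40% | 16% |
| 24 | 67% | 50% | 25% |
| 36 | 77% | 63% | 40% |

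**Step 5: definitions side by side.**
- OS origin: treatment or first medication in the synopsis, section 2 and 10.2; randomization in 7.1.2 only.
- DoR: progression or death in 10.2; incomplete in the synopsis, section 2 and 7.1.2.
- PFS: progression or death from start of treatment in the synopsis, section 2 and 10.2; 7.1.2 only names it.

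**Step 6: contact interval after progression.** Section 3.1 gives both 12 and 8 weeks. Section 3.5 gives 12 for all patients. Section 6.5 and the flow chart's survival note give 8 for patients who have progressed.

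**The case against.** The best defence is that 3.6 is loose wording. The protocol sometimes writes study where it means study treatment: 3.5 places the end-of-treatment visit within 4 weeks of the end of the study and then follows patients for 3 years, and 6.3 is similar. On that reading 3.6 describes the end of treatment and nothing is truncated. This is plausible, but no text says so. Section 3.6 carries the end-of-study heading and differs from the synopsis statement on the same subject.

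Several stronger inferences are tempting, and the documents do not support them:
- **That PFS is mis-defined.** Its definitions agree; it is only exposed to truncation.
- **That deaths will be censored in DoR.** Section 7.1.2 contains no censoring rule, and its sentence has lost the second event rather than excluded it. The only stated rule, in 10.2, counts death as an event.
- **That 7.1 overrides 10.2.** The sentence in 10.4 is a cross-reference, and 7.1 cannot govern alone because it does not define PFS. No randomization date will exist, so that word looks like a carry-over and is unlikely to change an analysis.
- **That all late enrollees get no PFS follow-up.** The loss is total only for the last enrolled patient. Responders may also continue beyond 12 months, which could delay closure.
- **That 24 months of OS are lost in general.** That figure applies after a full year of treatment. Patients who stop early lose closer to 12 months, and 6.5 does not cover everyone.
- **That imaging is in general disarray.** Note 17, 7.2 and one sentence of 3.1 agree on the interval after cycle 6; one other sentence of 3.1 and section 6.2 do not.

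**Conclusion.** The point stands as a set of contradictions in current text that bear on the secondary time-to-event endpoints. If 3.6 is applied, the last enrolled patient loses about 34 months of observation (13.8 against 48 months from first dose after a year of treatment), and earlier enrollees lose less. If 6.5 is applied, patients who progressed and started new treatment lose 12 months plus their time on treatment, up to 24 months within the planned year. Both sizes rest on 3.6 or 6.5 being treated as operative; the protocol does not say which text prevails. The event-free and survival percentages are illustrations under exponential assumptions.

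The OS origin and the DoR sentence in 7.1.2 are wrong as written but correctly stated in 10.2. The primary ORR endpoint, the sample size and the two-stage decision rule are unaffected. The protocol should be corrected; the point does not threaten the main conclusion.

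**What to change.** - In 3.6, adopt the end-of-study definition already in the synopsis.
- Align 6.5 with 3.5, so that every treated patient is followed for survival for up to 3 years after treatment.
- Reconcile the 8- and 12-weekly survival contacts across the flow chart note, 3.1, 3.5 and 6.5.
- Replace the OS wording in 7.1.2, and the DoR wording in the synopsis, section 2 and 7.1.2, with the 10.2 definitions.
- Reconcile the imaging interval after cycle 6 across flow chart note 17, 3.1, 6.2 and 7.2, so that all sites follow one stated schedule.

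The cost is a wording amendment. The practical burden is additional telephone survival contacts, which the flow chart already foresees.
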